## Abstract

Background

Self-medication (SM), a common practice globally, possesses a dual challenge of being a self-care strategy and a potential source of harm observed across all age groups. The study is being conducted to gauge the prevalence of SM of prescription drugs with their over-the-counter access, thus addressing the delicate balance between self-care and self-harm related to SM.

Material and methods

This ongoing convergent parallel mixed method study with quantitative and qualitative components will be conducted on a sample size of 180 subjects aged more than 18 years from an urban community. For the quantitative component, a semi-structured questionnaire will assess the prevalence of SM, types of medications used, reasons for self-medicating, and socio-demographic factors influencing these practices. Concurrently, qualitative interviews delve deeper into the beliefs shaping SM practices. Sampling will be purposive to capture diverse perspectives, with data analyzed using statistical tools.

Results

This study protocol will offer a comprehensive understanding of the prevalence and determinants of SM practices. The quantitative data provide numerical insights into SM trends, while the qualitative findings elucidate the nuanced factors driving individuals' SM choices.

Conclusions

A multifaceted view of SM practices will be provided, aiding in developing interventions to promote safe and effective self-care while mitigating the risks of self-harm through SM. Anticipated findings can include a widespread prevalence of SM amongst the general urban populace. Significant associations can also be expected to be found with various independent variables. The results will be instrumental in informing public health policies and healthcare practices toward enhancing patient safety and well-being.

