Research indicates that the decision to self-medicate is influenced by a multitude of personal, organizational, and environmental factors [12]. Self-care gained attention and notoriety during the COVID-19 pandemic when people started practicing hand hygiene, wearing masks, and performing self-testing at home [13]. SM is a practice observed across all age groups, but a particular focus is directed toward the elderly concerning treatment and medication issues. Numerous studies have highlighted the elderly as the predominant medicine consumers in many countries, a trend also observed in Iran. This heightened medication consumption among the elderly can be attributed to several factors, including the increased prevalence of various diseases associated with aging. Conditions, such as diabetes, cardiovascular disease, and cancer, are prevalent among a significant portion of the elderly population. Additionally, the presence of multiple chronic diseases concurrently, known as comorbidity, is widespread in this age group and often necessitates increased medication usage [7]. SM has long been a prevalent practice within the general populace. This phenomenon is driven by various factors, including the desire for self-care, empathy toward unwell family members, limited access to healthcare services, economic constraints, lack of awareness, misconceptions, widespread advertising, and the availability of medications outside of traditional medical outlets. Additionally, the literature suggests that reasons for engaging in SM include perceptions of illness severity, past experiences with similar illnesses, financial considerations, and difficulties accessing healthcare professionals [14,15]. SM practices should not be universally deemed harmful. OTC medications, available without a prescription, often offer convenience and cost savings for patients. Particularly in remote areas such as hill regions, tribal communities, and other underserved areas with limited access to healthcare professionals, SM remains a crucial recourse for addressing minor symptoms due to the scarcity of medical personnel [16]. Few studies have been conducted at a community level in India to evaluate the prevalence of SM practices. Such studies hold the potential to offer valuable insights into the motivations behind patient’s adoption of this practice. Moreover, they could aid policymakers and regulatory bodies in refining drug regulations, revising the list of essential medicines, and addressing safety concerns related to OTC medications. With this background, the study protocol aims to estimate the prevalence of SM of prescription drugs with their OTC access and the risk practice and identify potential factors that could influence SM practices in pharmacy outlets of Wardha along with reviewing policies pertaining to OTC and prescription drugs and identifying improvements to mitigate the risk practices.

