**Figure 1 FIG1:**
[figure not shown]
Schematic flowchart for mixed method study design

**Table 1 TAB1:** Description of the tool included in this study

Section	Details
Part A	Sociodemographic characteristics
	Age
	Place of residence
	Religion
	Marital status
	Level of education
	Occupation
	Family type
	Socioeconomic status (evaluated using Modified B.G. Prasad Scale)
Part B	Self-medication behaviors in the past year
	Patterns of self-medication (e.g., frequency, duration)
	Types of medications used
	Reasons for self-medication (e.g., convenience, cost, perceived need)
Part C	Pharmacist's perspective on self-medication practices
	Inquiry by a doctor to pharmacist
	Pharmacist's observations
	Customer behavior related to self-medication

Data analysis

All collected data will be analyzed using Statistical Package for the Social Sciences (IBM SPSS Statistics for Windows, IBM Corp., Version 23, Armonk, NY). Quantitative data will be presented as mean ± standard deviation, while qualitative data will be expressed as frequencies and percentages. Descriptive statistics will summarize and present sociodemographic characteristics, SM frequencies, patterns, and types of medications used. Measures, such as mean, median, and standard deviation, will be utilized to describe central tendency and variability. Inferential statistics will be employed to analyze relationships and associations between variables. Correlation analysis may explore the degree of association between factors such as age, socioeconomic status, and SM frequency. Furthermore, the chi-square test will assess the impact of demographic variables on SM practices. Group comparisons will be conducted using the student t-test. A p-value <0.05 will be considered statistically significant.

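### The effect of demographic factors on self-medication is assigned to an unadjusted chi-square test, which cannot tell a determinant from a correlate of one

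*Protocol article*

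**What the plan says.** All references are to the protocol article.

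- **Aim.** The Abstract promises a "comprehensive understanding of the prevalence and determinants of SM practices". The last paragraph of the Introduction sets out to "identify potential factors that could influence SM practices in pharmacy outlets of Wardha". The Results section expects to explore what influences SM and to feed recommendations for interventions and public health policy.
- **Method.** Under Data analysis, "the chi-square test will assess the impact of demographic variables on SM practices". Two further inferential methods are named: "Correlation analysis may explore the degree of association between factors such as age, socioeconomic status, and SM frequency", and "Group comparisons will be conducted using the student t-test". The criterion is "A p-value <0.05 will be considered statistically significant".
- **Candidate factors.** Table 1, Part A lists eight: age, place of residence, religion, marital status, education, occupation, family type and socioeconomic status ("Socioeconomic status (evaluated using Modified B.G. Prasad Scale").
- **Adjustment.** The article mentions no regression, stratification or other adjustment. The Limitations cover sampling bias, self-report and recall, but not confounding.

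**The concern.** A chi-square test of one factor against SM compares crude proportions. If socioeconomic status is associated with education, and education is what drives SM, the crude test for socioeconomic status picks up part of the education effect. The reverse can also happen: a real factor may be masked by another that works in the opposite direction. The Discussion itself names literacy, profession and low economic status together as factors linked to SM in similar studies, and one-at-a-time tests cannot say which of the three matters.

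At stake is the list of determinants the study will publish. An intervention aimed at a factor that is only a marker of another would be misdirected. The prevalence estimate is not affected.

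**Working it through.** **1. The plan's own figure.** The sample was sized for the precision of a prevalence: n = Z²P(1−P)/d² = 1.96² × 0.119 × 0.881 / 0.0025 = 161.1, so 161 reproduces. For dropout, 161/0.90 = 179 and 161/0.88 = 183, so 180 is reasonable. The calculation makes no provision for the determinant analysis.

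**2. Model for the illustration.** The documents give no association strengths, so every input here is an assumption except the 11.9% prevalence. There are two binary factors, education and socioeconomic status (SES), with 80 people in each SES group (160 analysed). SES has no effect of its own. P(low education | high SES) = 0.30. Low education raises SM by an odds ratio OR_E, and low SES is associated with low education by an odds ratio OR_A.

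- Low-education share in the low-SES group: odds = (0.30/0.70) × OR_A. With OR_A = 5 this gives 0.682; with OR_A = 8 it gives 0.774.
- SM in an SES group = share × p1 + (1 − share) × p0, where p0 and p1 are SM risks with high and low education.
- Chance of p < 0.05: Φ(z − 1.96) + Φ(−z − 1.96), with z = (q1 − q0)/√[q0(1−q0)/80 + q1(1−q1)/80], where q0 and q1 are SM in the high- and low-SES groups.

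**3. One case in full: OR_E = 2.5, OR_A = 5, 11.9% overall.** Then p0 = 0.0737 and p1 = 0.1660.

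- q0 = 0.30 × 0.1660 + 0.70 × 0.0737 = 0.101
- q1 = 0.682 × 0.1660 + 0.318 × 0.0737 = 0.137
- z = 0.0352/0.0511 = 0.69, so the chance of rejection is 0.102 + 0.004 = 0.106

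**4. All cases** (nominal rate 5%; true odds ratio for SES is 1).

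| OR_E, OR_A | Overall SM | q0 vs q1 | Crude OR for SES | Declared significant |
|---|---|---|---|---|
| 2.5, 5 | 11.9% (planned) | 10.1% vs 13.7% | 1.40 | about 10% |
| 2.5, 5 | 33% | 29.1% vs 36.7% | 1.41 | 17.5% |
| 2.5, 5 | 46% | 42.2% vs 50.7% | 1.41 | 19% |
| 3, 8 | 11.9% (planned) | 9.4% vs 14.4% | 1.62 | about 16% |
| 3, 8 | 36% | 30.4% vs 42.0% | 1.65 | 33% |
| 3, 8 | 50% | 43.5% vs 56.2% | 1.67 | 36% |

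Exact enumeration of the uncorrected chi-square test agrees to within 0.01 in every row. With the continuity correction the two 11.9% rows fall to about 6% and 10%, though that version of the test is itself conservative.

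**5. Does adjustment remove the problem?** A separate simulation used N = 180, two evenly split binary factors, a true odds ratio of 3 for one and none for the other, and 1,500 runs per setting. With correlations of 0.3, 0.5 and 0.7 between the factors, the crude chi-square test flagged the null factor in 12%, 20% and 36% of runs at 11.9% prevalence, and in 16%, 37% and 63% at 29.1%. A logistic model with both factors brought this back to about 5%.

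**6. What the sample can carry.** At 11.9% the expected number of SM cases is 161 × 0.119 = 19 to 180 × 0.119 = 21. Spread over eight factors at one term each, that is at most 21.4/8 = 2.7 cases per term, and fewer once multi-category factors are coded. At 29.1%, the lower end of the Indian range in the Introduction, 180 people give 52 cases, or 6.5 per term.

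**The case against.** The strongest reply is that this is a condensed article and a multivariable model may sit in an analysis plan not shown. The Data analysis section speaks broadly of relationships and associations, and does not say that its list of tests is complete. Much of the article is worded tentatively, and unadjusted association is a legitimate descriptive aim. This stands in part: a reader might infer that adjustment has been ruled out, and the text does not say so. But the concern does not rest on silence. The article positively assigns the question of impact to a chi-square test, and that assignment cannot deliver determinants.

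Second, the size depends on assumed inputs. That is right. A reader might take the 33-36% figure as the expected error rate, but it applies only if SM is far more common than the 11.9% used for planning. At 11.9% the inflation is roughly half as large, and smaller still with the continuity correction. The higher prevalences do lie in the 29.1-55% range cited in the Introduction, so they cannot be dismissed either.

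Third, a reader might go on to fault the t-test because most Part A factors have several levels, or because SM frequency is likely to be skewed. The text does not support this. It gives the demographic variables to chi-square, which handles several levels; it pairs SM frequency with correlation; it lists the median among its summaries; and it does not say how frequency is recorded or which groups the t-test compares. Nor does the article describe outlet numbers or structure from which a need for clustered standard errors could be argued.

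**Conclusion.** The point holds as a mismatch between aim and method: determinants are promised, and the test assigned to find them is unadjusted. Under the assumed association strengths, a factor with no effect of its own is declared significant about two to three times as often as the nominal 5% at the planned prevalence, and about three to seven times as often at prevalences of about 33-50%. The direction needs only that Part A factors are correlated and that at least one of them matters. The amount rests on assumptions, since the documents give no figures for either.

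It should be corrected before the analysis, but does not threaten the prevalence aim. A reader might also infer that an adjusted model would justify the word impact. It would not: adjustment deals only with measured factors, and the study is cross-sectional with purposive sampling.

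**What to change.** 1. Keep the chi-square tests as descriptive, and replace impact with association.
2. Base the determinant analysis on one adjusted model for SM: logistic, or modified Poisson with robust standard errors to give prevalence ratios, reported with 95% confidence intervals.
3. Prespecify a few Part A factors, such as age, education and socioeconomic status, entered together. If only about 19-21 cases arise, limit the number of terms or use Firth penalisation. Include sex only if it is collected: the Discussion names female sex as a factor, but Part A does not list it.
4. Settle which outcome is modelled. The inclusion criteria appear to require past or current SM. If that is enforced and no non-users are enrolled, a yes/no comparison is not possible, and the adjusted model should be applied to SM frequency or type, in a form suited to how that outcome is recorded.

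The cost is a few changed sentences, a little more analysis work on data already planned (unless sex is added), and slightly wider intervals for the adjusted estimates.

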## Results

The study is expected to provide insights into the prevalence of SM practices, explore the factors influencing it, elucidate the reasons driving individuals to self-medicate, and delve into experiences and perceptions to shed light on self-care behaviors in Wardha. It will help in providing recommendations for interventions to promote responsible self-care practices. These outcomes will not only inform strategies to enhance patient education on safe SM and improve access to healthcare services but also have policy implications for public health initiatives aimed at safeguarding individuals from the potential risks associated with SM while empowering them to make informed decisions about their health.

## Discussion

Many factors can lead people to take their own medication, including the need for self-care, empathy for sick family members, a lack of health services, poverty, misinformation, misbelief, and the accessibility of medications in places other than pharmacies. Research conducted in two phases in India has indicated the prevalence of SM among students to be 74.6% and 69.4% [17]. Similar studies suggest that literacy level, history of SM, profession, unavailability of medical insurance, lack of priority in consulting medical professionals, low economic status, the female sex, and staying in an urban setting were among the factors associated with SM practices [17]. Given the growing public health concerns around SM with prescription drugs and OTC access, this study focuses on risk practice prevalence, its use, its safety, and reasons for using it. On one side, the availability of medicines on an OTC basis improves access to healthcare for people living in settings lacking in resources or in places in need of adequate healthcare infrastructure. On the other, it increases the probability of severely harming one's health by the misuse of medications [7]. The dichotomy needs thorough investigation, allowing us to balance accessibility and responsible drug consumption. It is essential for individuals using medications to have appropriate medical comprehension regarding dosage, timing of administration, and potential ramifications of overuse, as inadequate information could lead to major repercussions, including antibiotic resistance, skin issues, hypersensitivity, allergies, and dependency. As it stands, regulations around the OTC availability of certain prescription drugs vary globally across jurisdictions. There is an urgent need to enhance awareness and enact regulations aimed at promoting prudent and safe practices regarding SM. There is a potential to encourage its rational use and mitigate the emergence of microbial resistance by fostering and improving its knowledge. Despite existing research on this subject, SM has slipped under the radar regarding receiving the attention it warrants as a research area. Moreover, most studies on this topic have been conducted in countries with vastly different healthcare systems and cultural contexts from that of India, rendering their findings potentially non-transferable. It is imperative to gather data on the prevalence of SM in India as well as explore their related factors to facilitate the enhancement of SM practices within the country.

Strength

The study focuses on SM practices in Wardha, encompassing diverse demographics through a cross-sectional design. It offers a comprehensive understanding by examining multiple factors influencing SM and can help frame interventions targeted toward promoting self-care practices that are holistic and responsible, ultimately resulting in improved healthcare services. This study can potentially influence public health policies and guidelines related to SM practices, highlighting the importance of regulating OTC medication and enhancing patient education.

Limitations

The study’s findings may be limited by sampling bias if the sample population is not representative of the broader adult population in Wardha, potentially impacting the generalizability of the results. The data collection through surveys and subject interviews could be prone to self-reporting due to the participants providing responses that are socially desirable or may inaccurately recall their self-medicating practices. There may also be temporal constraints for long-term trends, variability in policy enforcement effectiveness, and language and cultural factors may also impact the study's findings.

## Conclusions

It is anticipated that the study will shed light on the frequency of SM practices and investigate the factors influencing it. A multifocal perspective of SM practices, aiding in the advancement of interventions to promote safe and effective self-care while mitigating the risks of self-harm through SM, should be prioritized. By scrutinizing the factors influencing SM practices and their prevalence, this study aims to illuminate the balance between self-care and the potential harm associated with unsupervised medication use. The conclusions drawn from the analysis are anticipated to enrich our understanding of the complex interplay of cultural, individual, and societal factors that drive SM practices and drive meaningful change in healthcare delivery, strengthening health systems and safeguarding individuals from potential harm while harnessing the benefits of self-care practices.
